#### Implementation outcomes

##### Quantitative data

Descriptive statistics, including frequencies, means, and standard deviations for each item, will be used to summarize the CMDs’ responses to the self-administered questionnaires, providing an overview of the levels of adoption, acceptability, appropriateness, fidelity, feasibility, and sustainability. To complement this data, frequencies and percentages will be reported for the closed-ended questions in the PRITAH-evaluation forms.

##### Qualitative data

Data from the open-ended questions in the PRITAH-training evaluation forms will serve as input for the focus groups with the PRITAH-trainers and mangers of the organizations. To facilitate the analyses, the responses to the open-ended questions will be uploaded to the qualitative analysis software MAXQDA [50]. Analysis will be done through an iterative process involving multiple rounds of analysis and evaluation. A conventional content analysis approach will be used to explore the experiences and perceptions of the CMDs, trainers, and managers regarding the PRITAH-training and implementation [51, 52] This inductive approach avoids the use of predetermined categories, allowing the data to guide the categories and names for categories. The researcher will begin by familiarizing themselves with the data, reading all transcripts multiple times to obtain a sense of the whole. Subsequently, a line-by-line analysis will be performed to identify codes that capture key concepts. The researcher then notes initial impressions and thoughts. As this process continues, labels for codes emerge to form the initial coding scheme. These codes are then grouped into (sub)categories based on their relationships, creating meaningful clusters. This categorization process will be reviewed and refined in collaboration with the co-authors to ensure consistency and accuracy.

Data from the focus group meetings will be transcribed using an automatic speech recognition model (ASR), assisted by a research assistant [53]. The same analytical approach as for the open-ended questions will be used for this data. Since the findings from the open-ended questions serve as input for the focus groups, similar categories are likely to emerge. Although potential overlap, we will distinguish between two perspectives in which the questionnaires reflect the perspectives of CMDs, and the focus groups capture the perspectives of trainers and managers. As this remains an inductive process, the research team will be open to the emergence of new categories.

To assure trustworthiness, credibility is established through investigator triangulation, as two researchers will independently code the data from the open-ended questions and the focus groups. Additionally, the output from the open-ended questions serve as input for the focus groups, which can also be seen as a form of member checking [54].

##### Effect outcomes

Outcomes at the CMD level (attitude, subjective norms, perceived behavioural control, and intention) will be analysed with mixed (multilevel) regression, with linear regression for continuous outcomes and generalized linear regression (e.g., logistic, ordinal, gamma) for categorical outcomes. A total score per CMD or client per time point will be calculated for each outcome measure if multiple items measure the same construct and share the same response format (e.g. all items are binary or all items use a 5-point Likert scale). Repeated outcome measures are nested within CMDs. The fixed (predictor) part of the mixed model will include intervention (yes/no), region, care organization, and time point (t0, t1, t2; week 0/8/20), along with age, gender, educational level, work experience in care for older people, work experience in professional home care, current position, number of working hours, and hours working with individuals with dementia. Additionally, interaction of each predictor with time will be evaluated. The random part of the model will account for unexplained outcome variation between CMDs, which is allowed to change over time, by assuming an unstructured residual covariance matrix (marginal model). Predictor by time interactions will be deleted if not significant, with exception of the key interaction between intervention and time. Giving the nonrandomized treatment assignment, additional analysis will be (a) comparing treated and controls with respect to the baseline outcome measurement, adjusted for all abovementioned confounders, and (b) repeating the above mixed regression, but now with the baseline outcome as covariate instead of as repeated measures. This approach will help assess Lord’s paradox as a sensitivity/robustness analysis [43, 55].

All participating CMDs will be included into the analyses with all available data without imputing missing outcome measurements using maximum likelihood estimation. This approach is valid under the Missing At Random (MAR) assumption and is asymptotically equivalent to multiple imputation when using an appropriate imputation model [56]. Additionally, outcome missingness will be analyzed as a separate dependent variable using logistic regression (missingness at any given time point: yes/no) or mixed logistic regression for repeated measures (missingness at each time point), depending on the frequency and pattern of missing data. Covariates that predict missingness will be identified and incorporated into the primary outcome analyses.

Outcomes at the client level ((total score on the involuntary treatment questionnaire, and score per subscale (i.e., physical constraint, non-consensual care, the use of psychotropic medication)) will be analyzed in the same way as outcomes at the CMD level, with two modifications. First, predictors at the client level such as the client’s age, gender, living situation, informal caregiver, diagnosis, and presence of professional of homecare will be included as covariates. Second, unexplained outcome variation at the client as well as at the CMD level will be modeled with an unstructured covariance matrix [42].

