#### Sample

The study will take place within the region of South Limburg in the Netherlands, home to a population of 402,700 individuals [38]. Of this population, 27.4% are 65 years or older and 2.2% (8,660 individuals) are diagnosed with dementia [39, 40]. In 2020, CMDs supported approximately 33–41% (i.e. 2,858 to 3,551) of the people living with dementia at home in the region [41]. In this large region, 88 CMDs employed by four professional homecare organizations are responsible for the dementia care in this region. Each CMD manages a caseload of approximately 55 clients (i.e. PLWD) in a fulltime position or proportionally in a part time position. All 88 CMDs working in the region of South Limburg in the Netherlands are invited to participate in the study on the implementation of the PRITAH-intervention. The CMDs are employed across four organizations in two regions and are each assigned to a specific city district or village within that region. To avoid contamination, all CMDs within the same district or village are grouped together, resulting in multiple clusters. These clusters are then allocated to either the intervention or the control condition, ensuring that CMDs within a given cluster did not interact across conditions. The CMDs in the intervention group receive training in batches of 10 to 14 people, with a two-week delay between the start of each batch’s training. CMDs in the control group will provide care as usual, continuing their routine work. They will not receive any PRITAH components (policy, kick-off meeting and training, on-the-job coaching and consultation, and alternatives for involuntary treatment). Moreover, CMDs in the control group are free to address involuntary treatment according to their usual practice in their respective organization. CMDs on maternity leave, long-term sick leave, nearing retirement, or newly recruited during the PRITAH-implementation period are excluded from the study. In a nested design, as part of the effect study, all 88 participating CMDs will report on the use of involuntary treatment by formal and informal caregivers for 10 randomly selected clients within their caseload to provide insights at the client level. If a client drops out of the study due to discontinuation of care (i.e. institutionalization or end of life), they will be replaced by another randomly assigned client from the caseload of the CMD. Therefore, we anticipate collecting 880 responses on client level. See Fig. 1.

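### Deleting non-significant predictor-by-time terms removes adjustment of the intervention-by-time effect for weak to moderate confounders of change

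*Protocol article*

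**What the plan says.** All references are to the protocol article, section Data analyses, Effect outcomes, unless stated.

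- The fixed part of the CMD-level model holds intervention, region, care organization and "time point (t0, t1, t2; week 0/8/20), along with age, gender, educational level", followed by further CMD characteristics. That makes ten covariates besides intervention and time. The residual covariance over the three time points is unstructured.
- On interactions: "Additionally, interaction of each predictor with time will be evaluated", and then "Predictor by time interactions will be deleted if not significant, with exception of the key interaction between intervention and time".
- The client-level involuntary-treatment scores, which are the primary effectiveness outcome, "will be analyzed in the same way as outcomes at the CMD level, with two modifications". The two modifications are added client covariates and covariance at both client and CMD level. The deletion rule carries over.
- "Giving the nonrandomized treatment assignment, additional analysis will be" (a) a covariate-adjusted comparison of the arms at baseline and (b) the same regression "with the baseline outcome as covariate instead of as repeated measures". Both are labelled as a sensitivity or robustness check for Lord's paradox.

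**The concern.** The arms are not randomised, and the article itself calls the listed covariates confounders. A reader will assume that the reported intervention-by-time effect is adjusted for them. In this model, however, adjustment of that effect runs through the covariate-by-time terms, and these are what the rule deletes. A non-significant interaction among 88 CMDs does not show that the covariate fails to confound change. What is at stake is residual bias in the effect estimate, and a false-positive rate above nominal, while the covariates still appear in the model as main effects.

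**Working it through.** **Inputs.** From the article: 88 CMDs, three time points, ten covariates, unstructured covariance, the deletion rule. Not given, hence assumed: a 44/44 split, residual SD 1, within-CMD correlation 0.6, backward deletion at 0.05 (a two-degree-of-freedom test per covariate), true effect 0. The article states no power or effect figure to reproduce.

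**Step 1, algebra.** For a CMD in arm A with time-constant covariates X, and main effects only:

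Y_t = a_t + b_t·A + g'X + e_t, for t = 0, 1, 2.

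Subtracting baseline gives Y_t − Y_0 = (a_t − a_0) + (b_t − b_0)·A + (e_t − e_0). The term g'X cancels. The change equations then contain only {1, A}, which is nested in the baseline equation's {1, A, X}. Generalised least squares with an unstructured covariance therefore equals ordinary least squares on the changes, and b_t − b_0 is estimated by the raw difference in mean change. If X-by-time is kept, the change equations contain {1, A, X} and the contrast is adjusted.

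**Step 2, numerical check.** Complete data, intervention-by-time at T1 / T2:

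| Simulated data set | Raw difference in change | With covariate main effects | All covariate-by-time terms kept |
|---|---|---|---|
| 1 | 0.3875 / 0.1771 | 0.3875 / 0.1771 | 0.043 / −0.218 |
| 2 | 0.1712 / 0.5500 | 0.1712 / 0.5500 | −0.178 / 0.250 |

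**Step 3, departures from the exact case.**
- With about 20-36% of outcomes missing at random, the mean T2 estimate (truth 0) was 0.333 without covariates, 0.330 with main effects and 0.022 with all interactions.
- At client level (88 × 10 clients), the Sample section says of clients who leave care that "they will be replaced by another randomly assigned client from the caseload of the CMD". With no replacement, main effects moved the T2 estimate by 0. With 5-15% replacement per interval, a CMD-level main effect moved it by at most 0.002, and a client-level main effect by about 0.007-0.024 on average.

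**Step 4, the rule with one real confounder of change among the ten** (1,500 runs per row, T2 effect). The expected raw bias is arm difference × shift in change per SD of the confounder, for example 1.0 × 0.2 = 0.20.

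| Arm difference (SD) | Shift in change | Real term kept | Bias: raw | Bias: rule | Bias: all kept | False positives: rule | False positives: all kept |
|---|---|---|---|---|---|---|---|
| 0.5 | 0.1 | 18% | 0.048 | 0.030 | −0.001 | 6.5% | 4.7% |
| 0.5 | 0.2 | 55% | 0.099 | 0.028 | −0.003 | 8.9% | 6.0% |
| 0.5 | 0.3 | 88% | 0.150 | 0.011 | 0.002 | 5.5% | 4.8% |
| 1.0 | 0.1 | 17% | 0.099 | 0.063 | −0.003 | 9.6% | 5.2% |
| 1.0 | 0.2 | 54% | 0.199 | 0.060 | 0.001 | 11.3% | 4.7% |
| 1.0 | 0.3 | 87% | 0.304 | 0.030 | 0.008 | 8.3% | 4.9% |

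With no confounding of change, all ten terms were deleted in 60% of runs (0.95^10 = 0.60), and the estimate was then exactly the raw one.

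**Step 5, eight confounders**, each 0.3 SD apart between arms and each shifting change by 0.10 SD.
- All in the same direction: the raw bias is 8 × 0.3 × 0.10 = 0.24 SD. Under the rule about 14% of the real terms were kept, bias was about 0.17-0.18 SD and false positives were 16-17%. Keeping all terms gave bias 0.02 and 5%.
- Random directions: mean bias was about 0. False positives were 6.9% against 4.7% with all terms kept in one set of runs, and 8.4% against 5.7% in another.
- Weaker shift of 0.05 SD: 8.5% against 4.7% in the same direction, 6.8% against 5.9% in random directions.

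**The case against.** A reader might infer that the main estimate simply reverts to an unadjusted one, so that the effect claim has no protection against confounding. The article does not support that reading, for these reasons.

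- The fallback is a difference in change from T0. That already removes confounders whose influence is constant over time. Only confounders of change are exposed.
- The rule keeps significant terms. In Step 4 a strong confounder of change survived in 87-88% of runs.
- Analysis (b) is already planned, and covariate main effects do adjust there. Simulated as a regression of T2 on arm, baseline and all ten covariates, its bias was within −0.001 to 0.009.
- The 17% figure needs all eight assumed confounders to push the same way.
- Exact cancellation needs a linear model, complete data and time-constant covariates. The article also allows generalised models and replaces clients. The false-positive rates above are for CMD-level data. They were not computed for the client-level primary outcome, where client covariates rest on about 880 reports and their interactions may be tested with more power.

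All of this limits the size and reach of the point, and it stands. It does not defend the rule. Non-significance is still used as evidence of no confounding, and Step 3 shows that main effects hardly replace the deleted terms. Analysis (b) is presented as a check for Lord's paradox, so a gap between it and the main result could be put down to that paradox when part of it comes from the deleted terms.

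**Conclusion.** The point holds in limited form, as a should-fix. In the stated model, covariate main effects leave the intervention-by-time effect unadjusted: exactly in the linear complete-data case, approximately otherwise. Deletion by p-value therefore removes adjustment for weak to moderate confounders of change. With one such confounder (shift 0.1-0.2 SD) the bias was about 0.03-0.06 SD and false positives were 6.5-11.3%. Across the eight-confounder scenarios at 0.10 SD, false positives ran from about 7% to about 17%, against about 5-6% with all terms kept. Apart from the 88 CMDs and the covariate count, every input to these figures is an assumption, so they show a plausible range and do not predict this study's error rate. The point is not graver than should-fix, because effectiveness is the study's second aim, the implementation outcomes are analysed descriptively and are untouched, and (b) is already planned.

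**What to change.** Replace the deletion sentence, for both CMD-level and client-level models, with wording such as: a short list of confounders, fixed before the outcome data are seen, enters with its interactions with time, and these are retained regardless of significance. If the number of parameters is a worry, shorten the list in advance, or use a propensity score for allocation built from baseline covariates and entered with its time interaction. Report analysis (b) next to the main result, and say that its covariate main effects do adjust the intervention effect.

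The cost is analysis wording and some precision. With eight covariates the SD of the estimate rose from 0.225 to 0.240 (0.240 / 0.225 = 1.07, about 7%). An illustrative 14-column coding with balanced covariates gave about 10%, and imbalance would add to that. A binary or continuous covariate uses two degrees of freedom. Care organization, with four levels, uses 3 × 2 = 6, which is a further reason to keep the list short.

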### Ethical considerations

The Medical Ethical Committee of Zuyderland Medical Centre (METCZ20230080) determined on February 10th 2025 that this study was not subject to the Medical Research Involving Human Subjects Act. The PRITAH intervention itself and the small-scale implementation (feasibility and applicability) study was approved by the Medical Ethical Committee of Zuyderland Medical Centre (METC20180101) on August 30th 2018.

All participants in the study will receive an information letter to inform them about the aims and expectations of participating in the PRITAH- implementation study and will be asked to give their informed consent.

## Discussion

The current protocol describes the design of a quasi-experimental Hybrid Design Type-3 effectiveness-implementation study. Implementing new healthcare interventions into real-world practices can be challenging and time consuming [57]. Challenges regarding implementation often depends on the context in which the intervention is implemented, the individuals in the process, and the characteristics of the intervention itself [58, 59]. To address these challenges, conducting a context analysis is essential [58, 60]. Therefore, the current protocol was developed based on the results from a prior context analysis for the PRITAH-implementation (*to be submitted*). In two focus groups with policy staff members, a district nurse, CMDs, managers, and directors, we explored barriers and facilitators using the Consolidated Framework for Implementation Research (CFIR) [58, 60]. Overall, the context analysis revealed that both participating home care organizations support the implementation of PRITAH to prevent or reduce involuntary treatment at home.

Although randomized controlled trials (RCTs) are considered the gold standard in research, our study uses a quasi-experimental design. This type of design is more often recognized for their use in implementation studies where strict randomization may be infeasible or unfitting [61]. In our study, communication between CMDs within the same care organisation and region might induce treatment contamination. Hence, stratification based on region and district is necessary.

A Hybrid Type 3 Design is well suited for this study as the success of the PRITAH-intervention is determined both by how well it can be implemented into existing homecare settings and by its effect on client outcomes. Recommended conditions for a Type 3 Design, as outlined by Curran and colleagues, further support his approach The first condition is that, although the full effectiveness of the PRITAH intervention has yet to be established, research has demonstrated sufficient indirect evidence of its effectiveness, warranting further exploration of its implementation. Another supportive condition for this type of design is the legislation on involuntary treatment (Care and Coercion Act) and the in 2024 released guidelines, which creates a good momentum for implementation [35, 62].

The reliance on self-reported measures to assess both implementation and effect outcomes is a potential limitation. Self-reported data may be susceptible to different types of information biases, which could affect the reliability of the findings [63]. However, it should be emphasized that the target group of the current study involves PLWD living at home (i.e. behind closed doors). As clients are spread across individual households rather than concentrated in one setting, we depend on those who visit them. Therefore, self-reported data from CMDs represent the most feasible and informative approach to assess the outcomes. Importantly, while these data are reported by the CMDs participating in the PRITAH study, they concern the use of involuntary treatment by both formal and informal caregivers who are responsible for care in the client’s home situation. This provides a broader picture of involuntary treatment use beyond the CMD’s own practice. In addition, self-reporting encourages CMDs to reflect on their own practices and increases awareness of involuntary treatment use. Lastly, this approach is necessary given the logistical and time-consuming restraints of independent measurement (e.g. document analyses, interviews, observations), which might lead to the exclusion of participants as well as lower response rates.

We consider as a strength of this study the choice of CMDs as the study sample. CMDs play an important role in the care for PLWD at home by acting as a bridge between formal and informal care. Through their close collaboration with district teams, they are well positioned to disseminate the principles of the PRITAH-intervention and integrate them into daily practices. This central role makes CMDs key stakeholders, not only during the implementation but also in achieving the intervention’s intended effect on reducing involuntary treatment use in PLWD at home. Another strength of the study is the inclusive approach to ensure participation of all 88 CMDs working for four professional homecare organizations who meet the inclusion criteria. Therefore, within the study a broad range of experiences and practices is captured given the fact that each CMD has a large caseload. The diversity makes sure that the findings are more reflective of real-world settings, which in turn increases generalizability. Lastly, including all CMDs provides a more holistic view of the experiences towards the implementation, which is necessary for addressing barriers in future implementation efforts.

## Conclusion

Based on existing literature, previous research, and a context analysis this study aims to explore how to successfully implement the PRITAH-intervention and assess its effectiveness in preventing and reducing involuntary treatment. By using a quasi-experimental design and incorporating insights from a broad context analysis, we addressed the challenges of real-world implementation in this protocol. This protocol may serve as an example for the implementation of other complex interventions in long-term care settings for older people, offering a systematic and reproducible approach.

## Data Availability

No datasets were generated or analysed during the current study.

## Abbreviations

PRITAH: Prevention and Reduction of Involuntary Treatment At Home
CMD: Case Manager in the field of Dementia care
PLWD: People Living with Dementia
V&VN: Dutch Association of Nurses and Caregivers
AIM: Acceptability of Intervention Measure
IAM: Intervention Appropriateness Measure
FIM: Feasibility of Intervention Measure
ASR: Automatic Speech Recognition model
